### Sample size calculation

The sample size calculation is based on equivalence design for the primary endpoint- mortality rate of patients with abdominal compartment syndrome during acute pancreatitis. It is anticipated that decompressive laparotomy with temporary abdominal closure will lead to a mortality rate reduction from 60% of patients to 40%. Therefore, the expected reduction in mortality that was used for sample size calculation is 20%. With calculated 80% power of the study (beta error 0.20) and alpha error of 0.05 (two-sided) complete data from 47 patients per group will be necessary to demonstrate this effect, if it truly exists. Taking into account a 7% loss-to-follow up, a total of 2 × 50 patients have to be randomized.

Reported annual rate of treated patients with severe form of acute pancreatitis is about 250 (based on hospital data of Emergency Centre, Clinical Centre of Serbia, 3 affiliated hospitals of School of Medicine University of Belgrade and Military Academy), while the prevalence of abdominal compartment syndrome in this patient population is about 20%. Consequently, the total expected number of patients with abdominal compartment syndrome during acute pancreatitis in these 5 centres is about 50, annually. Based on this assumption, the expected study inclusion period would be ended in two years.

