**Conclusion:**

DECOMPRESS study is designed to reveal a reduction in mortality and major morbidity by using decompresive laparotomy with temporary abdominal closure in comparison with percutaneus puncture with placement of abdominal catheter in patients with ACS during SAP.

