## Discussion

The primary objective of present study is to compare two approaches aiming to try to determine the role of ACS in patients with SAP. During the last 15 years early surgical intervention in patients with SAP was not recommended and conservative treatment is a gold standard. Since recently, ACS during SAP attracted more attention and those patients are candidates for some type of intervention [14]. Surgical decompression may be the optimal solution [1,3,20-22,25], but mortality still remains high and it is resource-consuming and labor-intensive procedure, accompanied with increased risk of enteric fistulas, hemorrhaging, and possible greater incidence of infection of necrosis [5]. Percutaneous puncture with placement of abdominal catheter eliminates surgical intervention and open abdomen, but might not be sufficient in these very sick patients [3,4].

The very important step in the treatment of the ACS is the early prevention of the harmful effects [2-4,8,12-14]. Some of type of decompression should be performed as soon as diagnosis of ACS is established [14,16]. Although in routine clinical practice controversies persist regarding the timing, type of decompression procedure, and indications in patients with SAP [14]. Several investigators suggested that prompt recognition of ACS and adequate treatment could be crucial [3,4,14,16].

There are suggestions in the literature that percutaneous drainage should be the first step in the treatment of the patients with IAH and ACS [3,4,6,12,14,17-19]. Only patients who do not respond to this type of treatment should be candidate for surgical decompression [3,4,6,8,12]. Bearing in mind the high mortality rate among those patients, it remains unclear whether earlier surgical decompression will be able to reduce it. We hypothesized that open surgery, immediately after the diagnosis of ACS is established, could improve outcome of this patients. It is very important to stress that according to the study protocol, during the surgical intervention the retroperitoneum will be left untouched in order to avoid uncontrollable bleeding and possible opening of the route for infection of the necrotic area.

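### The sample size section names an equivalence design, but no margin is given and the hypothesis, effect size and test are all superiority

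*Protocol article*

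**What the plan says.** In the protocol article, the section *Sample size calculation* begins: "The sample size calculation is based on equivalence design for the primary endpoint". The sentences that follow describe something else. Laparotomy is expected to bring mortality down from 60% to 40%, the 20-point gap is called the expected reduction, alpha is 0.05 two-sided, power is 80%, and "complete data from 47 patients per group will be necessary to demonstrate this effect, if it truly exists". Allowing for 7% loss, 50 per group are to be randomised.

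The rest of the article agrees with those later sentences, not with the label:

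- Abstract, *Methods*: 100 patients are meant to show a fall from 60% to 40% with 80% power.
- Abstract, *Conclusion*: the study is "designed to reveal a reduction in mortality and major morbidity by using decompresive laparotomy with temporary abdominal closure".
- *Background*, last paragraph: the authors anticipate lower overall mortality with laparotomy.
- *Discussion*: "We hypothesized that open surgery, immediately after the diagnosis of ACS is established, could improve outcome of this patients".
- *Statistical analysis*: mortality is compared by Fisher's exact or chi-square test at two-sided 0.05 in the intention-to-treat population, and reported as a relative risk with its 95% confidence interval.

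No margin is given, and no rule compares a confidence interval with one.

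**The concern.** Equivalence and superiority reverse the null hypothesis. In a superiority trial p > 0.05 means that no difference was demonstrated. In an equivalence trial the claim is that the difference lies within a margin fixed in advance, and a non-significant test of difference is no evidence for that claim. One document cannot hold both positions for the same endpoint.

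What is at stake is how the primary result may be read. A non-significant mortality comparison is a likely outcome at the planned size (see the working). A reader who relies on the label could take it to mean that the two procedures have equal mortality. That reading would carry weight, because the Discussion describes laparotomy as the more burdensome procedure and cites suggestions that drainage should come first.

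**Working it through.** **Inputs, all from the protocol article.** Mortality 60% versus 40%; difference 0.20; two-sided alpha 0.05 (z = 1.960); power 80% (z = 0.842); 47 evaluable and 50 randomised per group; 7% loss; 1:1 allocation.

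**1. Does the stated 47 per group follow as a superiority calculation?**

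Pooled-variance formula, with mean rate 0.5:

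n = [1.960 × √(2 × 0.5 × 0.5) + 0.842 × √(0.24 + 0.24)]² / 0.20² = [1.386 + 0.583]² / 0.04 = 96.9, so **97 per group**.

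Other standard versions for the same inputs:

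| Version | n per group |
|---|---|
| Unpooled, two-sided | 94.2 |
| Arcsine, two-sided | 96.8 |
| Pooled with continuity correction, two-sided | 107 |
| Pooled, one-sided | 77 |
| Unpooled, one-sided | 74.2 |

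None gives 47. The figure equals half the unpooled value (94.2 / 2 = 47.1), which would fit a per-group number taken as a total, or a one-sample formula. That is an inference; the article does not show its formula.

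**2. Power at the planned size, 60% versus 40%.**

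- 47 per group: (0.20 × √47 − 1.386) / 0.693 = −0.021, so power is **49%**. By exact enumeration: chi-square 49%, Fisher 41%.
- 50 per group: (0.20 × √50 − 1.386) / 0.693 = 0.041, so power is **52%**. By exact enumeration: chi-square 54%, Fisher 46%.

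**3. What could the trial say about equality?**

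Half-width of the 95% confidence interval for the risk difference:

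- 50 per arm, arms at 60% and 40% (or both at 40% or both at 60%): 1.96 × √(0.48/50) = 0.192.
- 50 per arm, both at 50%: 1.96 × √(0.50/50) = 0.196.
- 47 per arm, both at 50%: 1.96 × √(0.50/47) = 0.202.

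So even with identical observed mortality of 50%, the interval only just excludes the 20-point effect with 50 per arm, and does not exclude it with 47.

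An example of a non-significant result: 29/50 deaths versus 20/50, a difference of 0.18. The test statistic is 0.18 / √(2 × 0.49 × 0.51 / 50) = 1.80, below 1.96. The interval is 0.18 ± 1.96 × √((0.2436 + 0.24)/50) = 0.18 ± 0.193, or about −1 to +37 points.

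**4. Illustration only: the size that equivalence would need.** The article gives no margin. Assume ±20 points, a true difference of zero, common mortality of 40% to 60%, and two one-sided 5% tests with 80% power:

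n = (1.645 + 1.282)² × 2p(1 − p) / 0.20² = 102.8 for p = 0.4 or 0.6, and 107.0 (fractionally above, so 108) for p = 0.5. That is **about 103 to 108 per arm**. Under the same assumptions 47 per arm would have about 23% to 26% power, and 50 per arm about 28% to 31%.

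**The case against.** The strongest reply is that this is a slip of one word. Equivalence is mentioned once, as a label on the sample size calculation. The sentences beside it, the abstract, the background, the discussion and the analysis section all describe superiority, and the article offers no margin or test by which anyone could declare equivalence. The label changes no test, population or number.

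Much of this stands. A reader might infer that the protocol licenses a conclusion of equivalence, or that the investigators plan one. The document does not support that: no such conclusion is announced and no rule for reaching one is given.

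It also stands that the low power is a separate error. It comes from the 47 per group and would remain if the word were deleted. Nor is the silence on how a non-significant result will be worded a fault in itself, since an article may leave that to the full protocol or analysis plan. A relative risk with its 95% confidence interval is already planned.

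What does not stand is that the word is harmless. It is a positive statement of design type for the primary endpoint, and it contradicts the hypothesis, effect and test. Condensing a protocol into an article does not explain it, and an analysis plan could not follow both. The 20 points cannot be taken as the missing margin either, because the article calls them the reduction it expects to find, not a difference to be ruled out.

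**Conclusion.** The concern holds as an internal contradiction. The sample size section names an equivalence design; everything else that defines the primary comparison is superiority. The label is wrong as written and should be corrected before results are interpreted.

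Its consequence is a risk of misreading, not an announced misuse. The risk is material because a test of difference at the planned size would be non-significant about half the time even if the assumed effect were real, and because 50 per arm gives an interval of about ±19 to 20 points, too wide to support a claim of equal mortality.

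The interval and power figures use the article's own rates and group sizes, plus equal 50% mortality where stated. The 103 to 108 per arm for equivalence rests on an assumed ±20-point margin and measures nothing the plan commits to.

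**What to change.** In *Sample size calculation*, replace the equivalence label with: superiority design (two-sided alpha 0.05). Add that a non-significant result will not be interpreted as equivalence, and that the 95% confidence interval already planned for the relative risk, together with one for the risk difference, will carry the interpretation. These wording changes have no operational cost.

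Relabelling alone would leave a false 80% power claim beside the word superiority. In the same edit, restate the power there and in the abstract: about 49% to 52% for 60% versus 40% with 47 to 50 per group, with about 97 evaluable per group needed for 80%.

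Stating this honestly is also only text. Enlarging the trial is a separate decision with a real cost: 97 / 0.93 = 104.3, so 105 per group or 210 in total. At the article's expected 50 eligible patients a year, that is 210 / 50 = 4.2 years of recruitment against the planned two, if every eligible patient is enrolled.

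If equivalence is truly intended, the plan instead needs a justified margin, a confidence-interval-based test and a sample size calculated for them.

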**Methods:**

One hundred patients with ACS will be randomly allocated to two groups: I) decompresive laparotomy with temporary abdominal closure or II) percutaneus puncture with placement of abdominal catheter. Patients will be recruited from five hospitals in Belgrade during two years period. The primary endpoint is the mortality rate within hospitalization. Secondary endpoints are time interval between intervention and resolving of organ failure and multi organ dysfunction syndrome, incidence of infectious complications and duration of hospital and ICU stay. A total sample size of 100 patients was calculated to demonstrate that decompresive laparotomy with temporary abdominal closure can reduce mortality rate from 60% to 40% with 80% power at 5% alfa.

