### Randomization

The study statistician generated and administrated 1:1 allocation randomization arrangement for the 5 study hospitals. Patients will be randomly assigned to group A (decompressive laparotomy with temporary abdominal closure) or group B (percutaneous puncture with placement of abdominal catheter) as shown in the flow-chart (Figure 1.). We did not stratify hospitals by procedure-volume or teaching status since all hospitals are under supervision of Medical Faculty of University of Belgrade, and the assumption is that hospitals are similar.

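### 47 patients per group gives about 50% power for mortality of 60% versus 40%, not the stated 80%; the stated inputs need 95 to 97 per group

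*Protocol article*

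**What the plan says.** The Sample size calculation section expects decompressive laparotomy to bring hospital mortality down from 60% to 40% and says that this 20-point difference was used for the sizing. It sets power at 80% and alpha at 0.05, two-sided. On that basis it says that "complete data from 47 patients per group will be necessary to demonstrate this effect, if it truly exists". It then adds patients for attrition ("Taking into account a 7% loss-to-follow up") and arrives at 2 × 50 randomised.

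The Methods paragraph of the abstract makes the same claim for 100 patients in total, namely that the trial is sized to show that laparotomy "can reduce mortality rate from 60% to 40% with 80% power at 5% alfa".

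The Randomization section fixes 1:1 allocation. The Statistical analysis section compares the two mortality proportions by Fisher's exact or chi-square test at a two-sided 0.05 level.

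**The concern.** All the inputs of the calculation are printed beside its result, and they do not fit together. A 20-point difference centred on 50% mortality is the case of largest binomial variance, and fewer than 50 patients per arm is well below what 80% power requires there.

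This is the primary endpoint, mortality, in a trial of a major open operation against a catheter. Ethics committees, centres and readers are told that the chance of missing a true 20-point reduction is 20%. If that chance is really near one half, a non-significant result says little about whether laparotomy saves lives. The printed 80% would invite readers to take it as evidence of no benefit.

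**Working it through.** **Inputs.** Mortality p1 = 0.60 and p2 = 0.40, difference 0.20, two-sided alpha 0.05 (z = 1.960), power 80% (z = 0.842) and 47 evaluable per group, all from Sample size calculation; 1:1 allocation from Randomization; Fisher's exact or chi-square test from Statistical analysis. No input had to be assumed.

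**Attempt to reproduce 47 per group**

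- Unpooled variance: n = (1.960 + 0.842)² × (0.6×0.4 + 0.4×0.6) / 0.20² = 7.849 × 0.48 / 0.04 = 94.2, so 95 per group.
- Pooled variance: n = (1.960×√0.50 + 0.842×√0.48)² / 0.04 = (1.386 + 0.583)² / 0.04 = 96.9, so 97 per group.
- Arcsine: 96.8, so 97 per group.
- Continuity-corrected, which is closer to Fisher's test: 106.7, so 107 per group.
- One-sided alpha 0.05, which the protocol does not use: 74.2 unpooled or 76.2 pooled, so 75 to 77 per group.

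None of these gives 47. Two slips do:

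- reading the per-group requirement as the total: 94.19 / 2 = 47.09;
- counting the variance of one arm only: 7.849 × 0.24 / 0.04 = 47.09.

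The two cannot be told apart from the result, and each leaves half the required number.

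**Power that the planned numbers deliver for 60% versus 40%**

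Normal approximation, pooled: power = Φ[(0.20×√n − 1.960×√0.50) / √0.48].

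- n = 47: Φ[(1.371 − 1.386) / 0.693] = Φ(−0.021) = 49.1%.
- n = 50: Φ[(1.414 − 1.386) / 0.693] = Φ(0.041) = 51.6%.

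The exact figures come from summing binomial probabilities over all possible tables.

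| Evaluable per group | Normal approximation | Exact, uncorrected chi-square | Exact, Fisher |
|---|---|---|---|
| 47 | 49.1% | 49.5% | 41.1% |
| 50 | 51.6% | 54.3% | 46.2% |
| 97 | 80.0% | 80.7% | 76.4% |

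**Effect for which 80% power does hold.** From 60% control mortality (pooled approximation), 50 per group reaches 80% power at about 32%, a 28-point reduction. With 47 per group it is reached at about 31.5%, or 28.5 points.

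**The planned effect, observed exactly.** With 30/50 against 20/50 deaths, the uncorrected chi-square is 4.00 (p = 0.046) and Fisher's test gives p = 0.071. The hypothesised result itself would sit on the border of significance.

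**Attrition.** 47 / 0.93 = 50.5, so strictly 51 rather than 50 per group. This is immaterial. For the correct requirement, 95 / 0.93 = 102.2 and 97 / 0.93 = 104.3, so 103 to 105 randomised per group, or 206 to 210 in total.

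**The case against.** The best defence is that the section calls the calculation an equivalence design, so a superiority formula might be the wrong yardstick. That does not rescue the figure. No margin is given, and the same paragraph sizes the trial to demonstrate a reduction. If a 20-point margin and equal true rates of 40% to 60% are assumed, a non-inferiority calculation needs 75 to 99 per group and two one-sided tests need 103 to 132. The log-rank comparison is no way out either. It is described as additional, and it would need 92 to 98 deaths, against about 50 expected among 100 patients at an average mortality of 50%.

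The article's condensed form does not help, since inputs and result are printed together and no further detail could make them agree. Recruitment is a fair reason for stopping at 100: the protocol expects about 50 eligible patients a year. It explains the number but does not make the stated power true.

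Three points on the other side do stand. The protocol shows no derivation, so the halving is an inference about the cause; the shortfall itself is not. Second, the primary endpoint is fixed at discharge or death, so near-complete data on 50 per arm is plausible. Power with an uncorrected chi-square would then be 54%, and the chance of a significant result is better described as about even than as worse than even. Third, the choice between chi-square and Fisher's test is a separate matter. The where-appropriate rule already points to chi-square when expected cell counts are 20 or more.

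**Conclusion.** The concern holds. With the protocol's own inputs, 47 evaluable patients per group give power of about 49% by chi-square and 41% by Fisher's test, and all 50 per group give 52% to 54% and 46%. The stated 80% is wrong in both the Sample size calculation section and the abstract. The chance of missing a true fall from 60% to 40% is roughly 46% to 59%, depending on the test and on attrition, and not 20%. The requirement is 95 to 97 evaluable per group, about twice the stated number.

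This rests on the stated rates, the two-sided 0.05 level and 1:1 allocation. It does not depend on the choice of variance formula, nor on how the error arose. It must be corrected, because it misstates what the primary analysis can show.

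**What to change.** Correct the Sample size calculation section and the abstract in one of two ways.

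- **Keep 2 × 50.** State that power is about 50% for 60% versus 40%, and that 80% power applies only to a fall from 60% to about 32%. Give the number that 60% versus 40% would require (95 to 97 evaluable, 103 to 105 randomised per group). Say in advance that a non-significant result will be read as inconclusive, with the planned 95% confidence interval for the relative risk showing which effects remain possible. The cost is wording and a less favourable stated power; no extra patients are needed.
- **Keep 80% power for 60% versus 40%.** Randomise 206 to 210 patients. At about 50 eligible patients a year, and if all are enrolled, recruitment takes about four years (210 / 50 = 4.2) instead of two, or needs more centres.

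Under either option, remove the equivalence label or reconcile it with the superiority aim. It would also help to name the uncorrected chi-square as the primary test. Expected counts will be about 20 or more per cell, and at the planned size Fisher's test costs a further 8 points of power (54.3% against 46.2% at 50 per group). This last step is advisable but not part of the correction.

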### Exclusion criteria

Patients will not be enrolled to the study if any of the following criteria are present: a) age < 18 and > 80 years; b) recent surgical interventions c) psychoses d) pregnancy e) previously history of chronic pancreatitis.

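### The two-year inclusion period assumes that every expected case of abdominal compartment syndrome is eligible, consents and is randomised, so it leaves no margin for reaching 100 patients

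*Protocol article*

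**What the plan says.** The second paragraph of the section Sample size calculation in the protocol article forecasts accrual. It starts from the severe cases treated in the five hospitals: "Reported annual rate of treated patients with severe form of acute pancreatitis is about 250". It then states that "the prevalence of abdominal compartment syndrome in this patient population is about 20" per cent. It multiplies the two: "the total expected number of patients with abdominal compartment syndrome during acute pancreatitis in these 5 centres is about 50, annually". The duration follows directly: "Based on this assumption, the expected study inclusion period would be ended in two years".

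The target is set in the paragraph before. There, "complete data from 47 patients per group will be necessary to demonstrate this effect", and after a 7% allowance for loss to follow-up "a total of 2 × 50 patients have to be randomized".

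The Methods paragraph of the abstract repeats the period without a condition: "Patients will be recruited from five hospitals in Belgrade during two years period".

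The section Exclusion criteria rules out patients with any of the following: "age < 18 and > 80 years; b) recent surgical interventions c) psychoses d) pregnancy e) previously history of chronic pancreatitis".

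**The concern.** The 50 a year is a count of patients who have ACS. It is not a count of patients who are eligible, agree to take part and are randomised. The forecast moves from the first count to the second with no reduction, although the article lists five exclusion criteria and the trial compares an open laparotomy with a catheter, a choice that some patients or families may not leave to chance. The 7% allowance does not help. It covers loss after randomisation and is already inside the 100.

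At stake is whether the stated size and the stated duration fit together. If recruitment were closed at two years, the trial would be expected to fall short of its own target. If it continued to 100, it would overrun the only duration that the article gives. A longer accrual period does not in itself bias the comparison, so this is a point about feasibility and consistent planning, not about the validity of the analysis.

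**Working it through.** **Inputs** (protocol article, Sample size calculation)
- Severe cases a year, five hospitals: about 250
- Share with ACS: about 20%
- Number to randomise: 2 × 50 = 100
- Stated inclusion period: 2 years
- Fraction of ACS cases eligible, consenting and randomised, f: not given

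**Step 1. Reproduce the plan's figure.**
ACS cases a year = 250 × 0.20 = 50.
Cases in two years = 50 × 2 = 100.
Years needed with every case enrolled = 100 / 50 = 2.0.
The stated two years is reproduced, but only with f = 1.

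**Step 2. Capture required.**
Required f = 100 randomised / 100 expected cases = 100%. There is no margin.

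**Step 3. Let f vary.** Patients in two years = 100 × f. Years to reach 100 = 100 / (50 × f) = 2 / f. The values of f are assumptions, shown as a range.

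| Assumed f | Patients in 2 years | Years to reach 100 |
|---|---|---|
| 1.0 | 100 | 2.0 |
| 0.9 | 90 | 2.2 |
| 0.8 | 80 | 2.5 |
| 0.7 | 70 | 2.9 |
| 0.6 | 60 | 3.3 |
| 0.5 | 50 | 4.0 |

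**Step 4. Chance variation.** If the two-year count is taken as Poisson with mean 100 × f (a further assumption), the probability of at least 100 patients is about 51% at f = 1.0, 16% at f = 0.9 and 2% at f = 0.8. Even with every case enrolled, two years is close to an even bet.

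**Step 5. How much more ACS would close the gap.** The share with ACS that gives 100 in two years is 50 / (250 × f) = 0.20 / f. At f = 0.8 this is 25%, and at f = 0.5 it is 40%. In the other direction, at the 36% incidence cited in the Background there would be 250 × 0.36 = 90 cases a year, and the capture needed would fall to 50 / 90 = 56%.

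**The case against.** The strongest reply is that the multiplication is correct and the article calls the result an expectation. Both inputs are given as approximate. The size is fixed as a number to be randomised, with two years as a projection from it, and nowhere does the article say that recruitment stops at two years whatever the count. A condensed article may also leave consent rates, screening yield and plans for slow accrual to the full protocol. All of this stands, and the mere absence of those details is not the complaint. The complaint is that the article carries the calculation through to a stated duration, and that duration follows only at full capture.

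Some of the text points towards more cases. The Background cites ACS incidences of 36% and 56% in other series and suggests that the complication has become more frequent. The section on treatment before randomisation introduces daily pressure measurement in all predicted severe cases, which may raise detection. It also keeps entry broad: neither late ACS nor a departure from the pre-randomisation protocol excludes a patient. These points count against any claim of impossibility. They do not restore the two years. The Background itself calls the cited series hard to interpret, the Conclusions name low incidence as a reason why no trials exist, and the article plans on 20%. The same section mentions transfers from referring centres, but the 250 already counts patients treated at these hospitals, and nothing shows transfers to be additional.

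A reader might go further and infer that two years cannot deliver 100 patients, or that the trial must close far short. The documents do not support that: it needs an enrolled fraction that they do not give, and at 90% the slip is only about 0.2 years. A reader might also take the 60% and 40% mortality as evidence of deaths before randomisation. Those are the anticipated in-hospital rates of the two randomised strategies, so they say nothing about losses before randomisation.

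**Conclusion.** The concern holds as a lack of margin. On the article's own planning figures, two years yields 100 randomised patients only if all 100 expected ACS cases are eligible, consent and are randomised. Nothing in the text says that the 50 a year is net of exclusions or refusal, and the listed exclusions make full capture unrealistic. Two years is therefore not expected to deliver the stated 100. With an assumed enrolled fraction of 90% to 50%, the expected shortfall at two years is 10 to 50 patients, or the period extends to between 2.2 and 4.0 years.

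This rests on taking the 250 and the 20% at face value. A higher true share of ACS would offset some or all of the loss, so the size of the gap is uncertain. The consequence is moderate: the forecast should be corrected, but the analysis is unaffected.

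**What to change.** 1. In Sample size calculation, multiply the 50 ACS cases a year by an explicit fraction expected to be eligible and randomised, give the basis for that fraction (for example, the hospitals' own records set against the exclusion criteria), and restate the expected inclusion period as 2 / f years. At 80% this is 2.5 years and at 60% it is 3.3 years. If the 50 is already net of exclusions, say so; refusal and missed cases would still need an allowance.
2. In the abstract's Methods paragraph, state that recruitment ends when the planned number has been randomised, and give the duration as an estimate.

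The cost is wording and a less favourable duration. The planned size, the analysis and patient management do not change.

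The duration must be recomputed if the sample size is corrected. For 60% against 40% at two-sided 5% and 80% power, the usual pooled formula gives (1.960 × √0.50 + 0.842 × √0.48)² / 0.20² ≈ 97 per group, not 47. With 7% loss, 97 / 0.93 rounds up to 105 per group, or 210 in all. At 50 cases a year that takes 210 / 50 = 4.2 years even with every case enrolled. The two corrections should therefore be made together.
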